### Participant timeline {13}

**Table Tabb:** 

Timepoint**	Study period			
	Enrolment	Allocation	Post-allocation	Close-out
	***− 1–3 days***	0	***Until catheter removal or hospital discharge***	***After catheter removal or hospital discharge***
**Enrolment:**				
**Eligibility screen**	X			
**Informed consent**	X			
**Demographic information**	X			
**Allocation**		X		
**Interventions:**				
***Conventional PICC***			X	
***Tunnelled PICC***			X	
**Assessments:**				
***Demographics***	X			
***Laboratory test***	X			
***Procedure details***			X	
***Procedure-associated complications***			X	
***Delayed complications***				X

### Sample size {14}

According to previous reports about PICC, infection rates range from 0.6 to 7.4% [1, 3–5]. In a previous retrospective study, the CLABSI rate of tPICC was 2.6% [13]. The sample size was calculated by assuming the same infection rate in this trial to verify the prior retrospective study result. In this trial, 2 × 677 participants are needed to prove a reduction of the infection rate from 6.2 to 2.6% for the primary outcome, at a two-sided α level of 0.05 and statistical power of 90%. A total of 1694 participants will be included in this study to account for a 20% dropout rate (PASS, version 16, NCSS statistical software). Data will be analysed on an intention-to-treat basis according to their originally assigned group.

### Recruitment {15}

According to the inclusion and exclusion criteria, all hospitalized patients requesting PICC will be potential candidates in this study. Physicians independent of this study will discuss the necessity of PICC with the participants. If the participants agree with catheterization, their physicians will consult with interventional radiology via an electronic medical record system. Investigators (interventional radiologists or clinical research coordinators) will review the participants’ medical records, and interventional radiologists will visit their wards to obtain informed consent. When obtaining informed consent, each candidate will have respectful discussions to ensure prudent decisions for the patients. A total of 339 patients will be enrolled from each of the five institutes by non-competitive recruitment.

### Assignment of interventions: allocation

#### Sequence generation {16a}

Randomization numbers will be generated by the R program (blockrand function in the package ‘blockrand’) using a 1:2 to 1:6 random block. An independent statistician generated multiple datasets, and an independent research organizer (Medsoft, Hwasung Gyeonggi, Korea) will apply one of the datasets to the electronic case report form (e-CRF) while blinded.

#### Concealment mechanism {16b}

Just before the procedure and after aseptic skin preparation, a circulating nurse who is not part of this trial will access the secure, password-protected, online-randomized database. The nurse will inform the investigator that the subject is in the cPICC or tPICC group.

#### Implementation {16c}

An independent statistician will create the computer-generated block randomization list. Then, each eligible participant with informed consent will be sent to the angiography suite and randomly assigned to a group immediately before the procedure by an independent circulating nurse in the angiography suite.

### Assignment of interventions: blinding

#### Who will be blinded {17a}

There is an unavoidable risk of bias in this type of randomized controlled trial where the intervention cannot be blinded to interventionists, participants, or care providers. However, this study has a single-blind characteristic due to following reasons. Participants can only presume their procedure on the grounds of their scar, but they cannot be assured about their group because procedures will be performed under aseptic drapes that screen the patient’s visual confirmation. It is difficult to know whether a tunnel is made or not because they are subcutaneous, and multiple skin incisions can also be made for conventional PICC. Furthermore, the interventionist will not confirm their group. As for care providers, mainly ward nurses can also presume the group but cannot be assured of the allocations for the same reasons as the participants. Outcome assessors will be blinded to allocation. The e-CRF on assignment will not be accessible to outcome assessors. Data analysts will be blinded until the end of the study.

#### Procedure for unblinding if needed {17b}

This study is unblinded.

### Data collection and management

#### Plans for assessment and collection of outcomes {18a}

In line with the pragmatic study, the participants will be treated for their condition according to the initial treatment plan. Daily physical examination and laboratory tests will be performed on a treatment schedule. Blood culture and laboratory testing will be performed as usual management when the participants have a symptom or sign of infection. Laboratory tests include white blood cell count with differentiation, erythrocyte sedimentation rate, and C-reactive protein level.

#### Plans to promote participant retention and complete follow-up {18b}

This study plans to enrol hospitalized patients, and adverse events (AEs) will be evaluated during hospitalization. We have no plan to promote retention.

#### Data management {19}

All data will be secured in an independent online server (Medsoft) outside hospitals. The investigators will be responsible for all data entry and management. At least two investigators will check all data.

#### Confidentiality {27}

All collected data will be coded with a code number, the only reference to participants’ identification during the study period to maintain anonymity. Informed consent forms will be secured in a locked cabinet in a password-locked secure place in each hospital. Data will be stored for 3 years after the end of this study according to the Enrollment Decree of the Bioethics and Safety Act of Korea. All data will be destroyed after that period, but data storage extension will be possible with Institutional Review Board (IRB) permission.

#### Plans for collection, laboratory evaluation, and storage of biological specimens for genetic or molecular analysis in this trial/future use {33}

Necessary laboratory blood tests and cultures will be performed depending on the clinical situation

### Statistical methods

#### Statistical methods for primary and secondary outcomes {20a}

Independent sample *t*-tests or Mann-Whitney *U* tests (continuous variables) and chi-square or Fisher’s exact tests (categorical variables) will be used to compare the two study groups. Data will be examined by cluster analysis, including the hospital level and ICU vs. general wards. The infection (CLABSI) rates will be reported as incidence per 1000-catheter dwelling days [16]. The rate ratio of both groups and 95% confidence interval and the *p*-value will be calculated by exact rate ratio test assuming Poisson counts. Cox proportional hazards regression will be used to estimate adjusted hazard ratios and 95% confidence intervals (CIs) for ‘time to infection.’ Hazards ratios with 95% CIs will be calculated for every complication. A *p*-value less than 0.05 will be considered significant.

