#### Outcomes {12}

The primary outcome is the effect of subcutaneous tunnelling in PICC placement on the rate of CLABSI. We will use the National Healthcare Safety Network surveillance definition [15]. CLABSI will be defined as a laboratory-confirmed bloodstream infection where the PICC is in place for more than 48 h and must meet both of these criteria: participants have a recognized pathogen identified from one or more blood specimens by culture- or non-culture-based microbiologic test, and organisms identified in the blood are not related to an infection at another origin (e.g. mucosal-barrier injury). A board-certified infection disease specialist will diagnose CLABSI at each institution, independent of this study for blinding.

The secondary outcomes include rates of local infection and bleeding from exit sites, extra procedure time for subcutaneous tunnelling, and technical success, defined as the rate of successful catheter tip placement to the cavoatrial junction. The local infection will be defined as one or combined symptoms followings: insertion site swelling with tenderness, local heating sense, or pus. Bleeding from exit sites will be marked when PICC cannot be kept in place due to continuous bleeding. Minor oozing causing dressing change will not be counted as this outcome. We will divide technical success into two categories. If there is a failure in puncturing the target vein or placing the catheter to the cavoatrial junction, we will define it as ‘impossible PICC.’ In case of subcutaneous tunnelling failure after target vein puncture, we will explain it as ‘impossible tunnelling.’

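### The 90% power is for a comparison of patient proportions, but the test tied to CLABSI is a rate ratio per catheter-day, with about 87–88% power at 677 per arm, and no analysis is named confirmatory

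*Protocol article*

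**What the plan says.** Three sections of the protocol article bear on this.

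- **Outcomes {12}** fixes no scale: "The primary outcome is the effect of subcutaneous tunnelling in PICC placement on the rate of CLABSI". A rate could be a share of patients or events per catheter-day.
- **Sample size {14}** uses shares of patients. It gives 677 per arm and says that these "participants are needed to prove a reduction of the infection rate from 6.2 to 2.6% for the primary outcome". The error rate is set at 5%, two-sided, and the power at 90%. The section then raises the total: "A total of 1694 participants will be included in this study to account for a 20% dropout rate".
- **Statistical methods for primary and secondary outcomes {20a}** opens with a general sentence under which chi-square or Fisher's "exact tests (categorical variables) will be used to compare the two study groups". It next says that CLABSI is reported per 1000 catheter-days, and that the rate ratio, its interval and its p-value "will be calculated by exact rate ratio test assuming Poisson counts". It continues: "Cox proportional hazards regression will be used to estimate adjusted hazard ratios" with confidence intervals, for time to infection. One significance threshold of 0.05 closes the section.

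No section says which of these analyses decides the trial.

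**The concern.** The trial is sized on one scale and, on the plainest reading, tested on another. A proportion ignores how long each catheter was in place; a rate per catheter-day divides by it. Follow-up ends at catheter removal or discharge, so exposure varies between patients and may differ between arms.

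Two things are at stake. The stated power may not be that of the test that will be run. And because nothing says which scale is confirmatory, a borderline result could be called significant on one scale and not on the other.

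**Working it through.** **Inputs from the protocol.** Risks p1 = 0.062 and p2 = 0.026; two-sided α = 0.05 (z = 1.960); power 90% (z = 1.2816); 1:1 allocation; 677 per arm; 20% dropout; 1694 in total.

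**Step 1: reproduce the stated sample size.** Two-proportion z-test, unpooled variance:

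n = (1.960 + 1.2816)² × [0.062 × 0.938 + 0.026 × 0.974] / 0.036²
= 10.507 × 0.08348 / 0.001296 = 676.8, so 677 per arm.

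The pooled form, which corresponds to the uncorrected chi-square test, gives 680, and 89.9% power at 677. For dropout, 677 / 0.8 = 846.25, so 847 per arm and 1694 in total. The protocol's figures reproduce, and no dwell time or event rate enters them.

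**Step 2: power of the exact rate-ratio test.** Conditional on the total number of events, the conventional-arm count is binomial with probability equal to that arm's share of catheter-days. The two-sided p-value is twice the smaller tail. Assumptions: Poisson counts, expected events equal to n × risk, and equal total dwell (share 0.5).

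| Per arm | Expected events (conventional + tunnelled) | Power |
|---|---|---|
| 677 | 42.0 + 17.6 = 59.6 | 87.3% |
| 847 | 52.5 + 22.0 = 74.5 | 93.7% |

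With binomial instead of Poisson counts the figures are 87.8% and 94.2%. Power reaches 90% at about 740 per arm, so with 847 enrolled it is kept if losses stay below about 1 − 740/847 = 13%.

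For comparison at 677 per arm, exact enumeration gives 91.0% for uncorrected chi-square and 88.5% for Fisher.

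**Step 3: sensitivity to dwell time.** The protocol gives no dwell time, so the exposure ratio (tunnelled over conventional) is varied over an assumed range with the patient risks held at 6.2% and 2.6%. The implied rate ratio is (0.026/0.062) / exposure ratio = 0.419 / exposure ratio.

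| Exposure ratio | Implied rate ratio | Power at 677 | Power at 847 |
|---|---|---|---|
| 0.8 | 0.52 | 61% | 72% |
| 0.9 | 0.47 | 76% | 86% |
| 1.0 | 0.42 | 87% | 94% |
| 1.1 | 0.38 | 93% | 97% |
| 1.2 | 0.35 | 97% | 99% |

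The sensitivity runs both ways: shorter dwell in the tunnelled arm costs power and longer dwell adds it.

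**Step 4: can the choice change the verdict?** Take 677 per arm, equal exposure, and 34 against 19 events. Chi-square gives p = 0.036, Fisher p = 0.049, and the exact rate ratio p = 0.053.

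**Step 5: error rate if every analysis counted.** A null simulation (4.4% risk in both arms, assumed gamma-type dwell with mean 20 days, 8000 runs) counted trials in which at least one of chi-square, the exact rate ratio and a Cox score test gave p < 0.05. The result was 6.0% at 677 per arm and 5.6% at 847.

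**The case against.** The best defence is that the methods section already points to one test. The chi-square/Fisher sentence is general and does not mention CLABSI. The Cox sentence promises hazard ratios and intervals, not a p-value. Only the exact rate-ratio test follows directly on CLABSI with a p-value. An article condenses the full plan, and a SAP that is not shown may name the primary analysis. With equal dwell the shortfall is about 3 points, and at the planned 847 per arm power is above 90%.

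Most of this stands, and it rules out three stronger readings that a reader might infer.

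- **That CLABSI is tested three times at 5%, with material inflation.** The text does not say so. Even if all three analyses were counted, the tests are so highly correlated that the excess is about one point with equal dwell.
- **That the 90% belongs to a test the trial never uses.** The z-test behind 677 is in effect the uncorrected chi-square, which is listed; 677 against 680 is only a variance convention.
- **That chi-square would badly inflate false positives.** Simulations with an equal daily hazard and 20% or 30% longer dwell in one arm put its rejection rate at about 11–13% or 20–21%. But that dwell difference is assumed, the protocol does not suggest one, and it does not name chi-square as the CLABSI test.

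The defence does not remove the mismatch. The missing primary label alone could be left to a SAP, but the sample size and methods sections put the same outcome on different scales in the text shown. If the rate-ratio test is the intended one, the power figure was not calculated for it.

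**Conclusion.** The point holds, at moderate severity. The 677 per arm and the 90% are correct for a comparison of patient proportions. They do not describe the exact rate-ratio test, the only one tied to CLABSI with a p-value: about 87–88% at 677 per arm and about 94% at 847, given equal total dwell and Poisson or binomial counts at the protocol's own risks. Under the assumed exposure ratios of 0.8 to 1.2, power at 677 spans about 61% to 97%, so the dwell assumption matters more than the 3-point shortfall. Whether dwell will differ between arms cannot be judged from the protocol.

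The lack of a designated confirmatory analysis matters mainly for borderline results, where the two scales can fall on opposite sides of 0.05.

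**What to change.** 1. In the statistical methods section, state that the exact rate-ratio test on CLABSI per catheter-day is the single confirmatory test at two-sided 5%. It is already attached to the outcome, so this changes no method.
2. Label any comparison of CLABSI proportions, and the Cox model, as supportive.
3. In the sample size section, keep the derivation of 677 but add the power of the confirmatory test: about 87–88% at 677 evaluable per arm and about 94% at 847, assuming equal dwell, with the range for unequal dwell or a stated expected dwell time for each arm.

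The cost is a few sentences and a slightly less favourable power figure at 677. No extra patients are needed. When the article was submitted, 700 patients had been recruited; no interim analysis is planned and analysts are to be blinded until the end of the study, so the choice could be fixed before results by arm were seen.

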**Methods:**

In this multi-institutional, prospective, non-blinded pragmatic randomized controlled trial, 1694 patients treated at five referral hospitals will be assigned to one of two parallel arms (conventional and tunnelled PICC groups) using computer-generated stratified randomization. The conventional group will undergo PICC placement by routine practice. In the tunnelled PICC (tPICC) group, additional subcutaneous tunnelling will be applied. Patients will be followed until PICC removal or the end of this study. The primary endpoint is whether subcutaneous tunnelling reduced the rate of CLABSI compared to the conventional method. The secondary endpoints are technical success rates, complications including exit-site bleeding or infection, and the procedure time between the groups.

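### A hazard ratio is prescribed for every complication, which mislabels events fixed at insertion and has no finite value when one arm has no events

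*Protocol article*

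**What the plan says.** The section on statistical methods for primary and secondary outcomes {20a} gives a general rule for group comparisons: "chi-square or Fisher’s exact tests (categorical variables) will be used to compare the two study groups", with t or Mann-Whitney tests for continuous variables. It then sets an exact Poisson rate ratio for CLABSI and a Cox model for time to infection, and adds: "Hazards ratios with 95% CIs will be calculated for every complication". No minimum event count and no exception by type of complication is stated.

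The participant timeline {13} has separate assessment rows for "Procedure-associated complications", marked under the post-allocation period, and "Delayed complications", marked under close-out.

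Outcomes {12} names two complications as secondary outcomes: "The secondary outcomes include rates of local infection and bleeding from exit sites, extra procedure time for subcutaneous tunnelling, and technical success". On bleeding it says: "Bleeding from exit sites will be marked when PICC cannot be kept in place due to continuous bleeding"; minor oozing is not counted. No expected frequency is given for local infection, bleeding or procedural complications.

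**The concern.** A hazard ratio compares event rates over time at risk. The timeline itself recognises a class of complications tied to the procedure. Those events occur before any dwell time has accrued, so there is no time axis along which to compare hazards. A second difficulty arises with sparse data: if one arm has no events, the Cox partial likelihood has no finite maximum, and neither the hazard ratio nor its usual interval exists.

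Complications are the counterweight to any reduction in CLABSI. The hazard ratio is the only effect measure with a confidence interval that the plan ties to them. Where it is mislabelled or undefined, the analyst must either print a number that does not mean what its label says, or choose a substitute after seeing the counts.

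**Working it through.** **1. The number per arm.** Inputs from the sample size section {14}: 6.2% vs 2.6%, two-sided alpha 0.05, power 90%, 20% dropout. With the unpooled normal approximation, n = (1.960 + 1.282)² × (0.062 × 0.938 + 0.026 × 0.974) / 0.036² = 676.8, so 677 per arm, as stated. Allowing for dropout, 677 / 0.80 = 846.25, so 847 per arm and 1694 in total, as stated. The checks below use 847 per arm.

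**2. Events fixed at insertion.** Let D = a + b events all be tied at one time, with n per arm. Under Breslow's handling of ties the partial likelihood is θ^a / (nθ + n)^D. Setting the derivative of its logarithm to zero gives a/θ = D/(θ + 1), hence θ = a/b. With equal arms that is exactly the risk ratio.

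The counts below are illustrative; none come from the protocol.

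- 42 vs 17 of 847: risk ratio 42/17 = 2.47; Cox with Breslow ties 2.47; Cox with Efron ties 2.51; odds ratio (42 × 830)/(17 × 805) = 2.55.
- 10 vs 5 of 847, second arm relative to first: risk ratio 0.500; Cox with Efron ties 0.499 (95% CI 0.17 to 1.46).

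The model runs and the number is usable, but it is a risk ratio, and its small departures from the risk ratio come from how ties are handled.

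**3. An empty arm.** With 3 vs 0 events of 847, the Cox fit gave no finite estimate and no interval. Fisher's exact test on the same counts gave p = 0.25. The risk difference is also defined: 3/847 − 0 = 0.35 percentage points.

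**4. How often an arm would be empty.** Assume the same true risk p in both arms and let z = (1 − p)^847 be the chance that a given arm has no events. Then P(exactly one arm empty) = 2z(1 − z) and P(both empty) = z².

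| Assumed risk p | z | Exactly one arm empty | Both empty | At least one empty |
|---|---|---|---|---|
| 0.1% | 0.4285 | 49% | 18% | 67% |
| 0.2% | 0.1835 | 30% | 3.4% | 33% |
| 0.3% | 0.0785 | 14% | 0.6% | 15% |
| 0.5% | 0.0143 | 2.8% | 0.02% | 2.8% |
| 1% | 0.0002 | 0.04% | about 0 | 0.04% |

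With 677 per arm, the chance of at least one empty arm is higher: 76% at 0.1%, 45% at 0.2%, 6.6% at 0.5% and 0.2% at 1%.

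**5. Sparse but non-empty arms.** With D events split about evenly, the 95% CI runs from the estimate divided by F to the estimate times F, where F = exp(1.96 × 2/√D). This gives F = 5.8 for D = 5, 3.5 for D = 10 and 2.4 for D = 20. A finite ratio from very few events therefore says little.

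**The case against.** The strongest reply is that the same section already provides a safeguard. Chi-square or Fisher's exact tests cover categorical outcomes, and the secondary outcomes are worded as rates by arm, so crude risks and a test that tolerates empty cells are planned whatever happens to the hazard ratio. That is right and limits the damage. It does not supply an effect estimate with an interval, because Fisher's test as specified gives a p-value only. Choosing a particular interval method or sparse-data rule would normally be left to the analysis plan; the point here is that the article states a blanket rule that does not fit part of what it covers.

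Several stronger readings are tempting and should not be drawn:

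- **That several safety results will be meaningless or not estimable.** Only two complications are named secondary outcomes, neither is defined as fixed at insertion, and no rates are given. An empty arm becomes likely only at assumed risks of about 0.3% or less. A hazard ratio computed on insertion-time events is mislabelled, but it lies within about 2% of the risk ratio in the example above.
- **That exit-site bleeding cannot be analysed by Cox regression because it ends follow-up.** An event that ends follow-up is ordinary input to a survival model, and the bleeding definition does not place it at insertion.
- **That onset dates are not collected because delayed complications are marked at close-out.** The data monitoring section {21a} has catheter-related events checked during follow-up and entered in the e-CRF, and the harms section {22} describes daily checks of each case. The e-CRF is not shown, so missing dates are not established.
- **That a hazard ratio is prescribed for procedure time.** The abstract lists "technical success rates, complications including exit-site bleeding or infection, and the procedure time between the groups", which keeps procedure time apart from complications. It is a continuous outcome with its own tests.

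**Conclusion.** The point holds in limited form. The rule gives a wrong label to procedure-associated complications, and it prescribes a quantity that does not exist when one arm has no events. How often the second problem would arise cannot be settled from the documents: the 49%, 30%, 14% and 3% figures rest on assumed equal risks of 0.1%, 0.2%, 0.3% and 0.5% with 847 per arm, and the problem is negligible at 1% or above. Two features of the text make low counts plausible without proving them: bleeding counts only when the catheter cannot stay in, and the section on post-trial care {30} describes tunnelling as having no serious complications on record. What is missing in those cases is an interpretable estimate with an interval; a valid test remains. This is a secondary matter, but worth correcting because it concerns a stated rule and is cheap to change.

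**What to change.** Replace the sentence in {20a} with a rule of this kind: hazard ratios with 95% CIs are calculated for complications that arise during catheter dwell (local infection, exit-site bleeding, CLABSI) and have events in both arms. For procedure-associated complications, and for any complication with an empty arm or very few events, report n (%) by allocated arm with the risk difference and, where estimable, the risk ratio, using exact or Miettinen-Nurminen 95% CIs, alongside the Fisher test already planned. State the event count that defines very few before the data are unblinded.

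The cost is one sentence, reported to the IRBs and the registry as {25} requires for any protocol change. No new e-CRF field is needed. The downside is two effect measures in the complications table instead of one. Recruitment was still under way when the article was submitted and {33} does not bear on this; under {17a} the data analysts stay blinded until the end of the study, so the change can be made without knowledge of the results by arm.
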